## Method

### Study design

This is a single blind, two-arm feasibility RCT of FAB with conventional treatment versus conventional therapy alone for severe DED, including a qualitative process evaluation (figure 1 provides details of the study scheme). This trial is ongoing and open to recruitment at two participating sites: Bedford Hospital NHS Trust and Moorfields Eye Hospital London. Recruitment into the trial commenced in April 2018 and is due to finish by April 2019.

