### Intervention

#### Arm A—FAB plus conventional treatment

The patients will use FAB therapy alongside conventional therapy (artificial tears, ciclosporine drops or punctal plugs/cautery) as recommended by their treating ophthalmologist. Hands will be washed with soap and water, dried and then a fingertip of the hand will be wiped with an alcohol-based wipe and self-pricked using a standard diabetic lancet. The drop of blood produced as normal is applied to the lower fornix of the affected eye(s) with the lower lid pulled down slightly by the patient. The blood will be applied four times a day. A fresh finger will be used for each eye and blood wiped away with the alcohol-based wipe. Patients will be advised to keep nails short and to avoid nail varnish. The FAB intervention will be applied at least 15 min after any artificial tears and participants must not use drops for at least half an hour after this.

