### Outcome assessment

The primary outcome measure is the proportion of eligible patients approached who consent to and comply with the trial protocol. This will be assessed by: number of eligible patients within the study population and recruitment time frame, percentage of eligible patients accepted for randomisation, patient compliance with trial protocol measured as per self-reported adherence to intervention and percentage of patients completing study. The secondary outcomes include reduction in corneal inflammation (assessed by the Oxford corneal staining guide), patient pain and symptoms scores (assessed by the OSDI Score) and improvement in objective signs of DED as indicated by visual acuity, Schirmer’s test, tear break-up time, lower and/or upper tear menisci height measurement. Other secondary end points include patients’ QoL (assessed using the EQ-5D-5L Questionnaire), cost to the NHS and patient (assessed via use of additional NHS services and privately purchased over-the-counter treatments related to DED) and safety measure of pressure within the eye (assessed by IOP Score).

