### Data analysis

Detailed data validation will examine completeness, existence and accuracy of collected data to assess data quality and identify missing and conflicting data. Statistical analysis will be performed on an intention-to-treat basis ie, inclusion of patients randomly assigned, regardless of adherence, actual treatment received, and subsequent withdrawal of treatment and/or deviation from the protocol and per-protocol (ie, inclusion of those who completed the treatment as planned)^29^ and will be reported according to 2010 CONSORT guidelines.^30^ All statistical analyses will be completed using SPSS Statistics V.22.0.^31^ A value of p<0.05 will be accepted as statistically significant. Conforming to recommendations for feasibility studies, data analysis will be primarily descriptive, with means, SD and frequency counts calculated for all variables of interest.

Exploratory efficacy analysis will compare the primary outcome variables derived from the data collected at 8 weeks between the two arms using a marginal general linear model with robust standard errors, to allow for clustering by group. Secondary outcomes between the intervention and control groups will be compared at 4 weeks, 8 weeks and 12 weeks (4 weeks post-treatment). Safety outcome measures will include IOP rise and any reported infection. Secondary analyses of the primary outcome, controlling for baseline covariates, will be performed using proportional hazards regression models.^32^ Analysis of treatment discontinuation adjusted for clinical site, baseline status, and whether the patient is randomised to the FAB or control (conventional treatment only) group will be conducted. Any interaction between baseline status or regimen and treatment will also be assessed. Interactions between significant covariates and treatment effects will be assessed in the context of the proportional hazards models.

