#### Randomisation procedures

Randomisation will be carried out by the Anglia Ruskin Clinical Trials Unit (ARCTU) using the SEALED ENVELOPE randomisation service. SEALED ENVELOPE is a randomisation and online database service developed for clinical trial services. It is an internet-based system and will be set for this study by ARCTU in accordance with the protocol. Enrolled patients will undergo 1:1 block randomisation to Arm A or Arm B. The system stores the predetermined sequence of randomisation and this list is visible to neither the investigator nor the ARCTU staff. Once a patient has consented to take part in the trial, they will be randomly allocated either to Arm A to receive FAB and conventional therapy or to Arm B to receive conventional therapy only. The research nurse or fellow or designated staff will log on to a web browser application and enter the patient’s eligibility factors into the system. The treatment allocation will be sent to the research team who will make the necessary arrangements for the patient’s treatment plan.

The treating ophthalmologist in the clinic will prescribe and counsel all patients on the correct technique for conventional treatment. The unblinded research nurses will provide additional training to the patients on the method of delivering FAB, including the use of a training video. Patients will be advised by the research team to inform their ophthalmologist if they have been started on any new treatment during the trial period by other clinicians or themselves.

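### The 8-week model allows for clustering by an undefined "group" that does not fit individual randomisation, and its robust standard error is unusable whether group means arm or site

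*Protocol article*

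**What the plan says.** The Study design section states: "This is a single blind, two-arm feasibility RCT of FAB with conventional treatment versus conventional therapy alone for severe DED". Recruitment is at two sites. Allocation is by patient: "Enrolled patients will undergo 1:1 block randomisation to Arm A or Arm B" (Randomisation procedures).

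For the comparison of arms, the Data analysis section says: "Exploratory efficacy analysis will compare the primary outcome variables derived from the data collected at 8 weeks between the two arms". The method follows directly: "using a marginal general linear model with robust standard errors, to allow for clustering by group". The word *group* is not defined there. In the rest of the paragraph it refers to the randomised arms: "Secondary outcomes between the intervention and control groups will be compared at 4 weeks, 8 weeks and 12 weeks", and later "whether the patient is randomised to the FAB or control (conventional treatment only) group". In that last sentence clinical site is listed as a separate adjustment variable.

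The same section sets p<0.05 as the threshold for significance, and describes the analysis as mainly descriptive.

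The outcome named for this model is the primary one, which is measured on patients: "The primary outcome measure is the proportion of eligible patients approached who consent to and comply with the trial protocol" (Outcome assessment).

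**The concern.** A robust variance with clustering needs many independent clusters, each holding observations that may be correlated. The trial as described has no such structure at the level of a group. Randomisation is individual, patients apply the blood themselves, and no group delivery or shared therapist is mentioned. The sentence therefore names a clustering unit that the design does not supply.

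This is the model named for the 8-week between-arm comparison, and its results would be read against p<0.05. If an analyst followed the sentence literally, the standard error, interval and p-value would be meaningless. A false signal of benefit could then colour the decision on a definitive trial. The exemption for detail left to a fuller protocol or a SAP does not help here, because the article states the clustering unit and does not leave it open.

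**Working it through.** **The plan's own figures.** The article gives no standard error, intracluster correlation or power for this model, so there is no stated result to reproduce. The only computable figure nearby is the recruitment target: 52/(1 − 0.10) = 57.8, so 58, against a stated 60. The gap is 2 patients, and the point below does not affect the target.

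**Inputs.** 26 patients per arm (Sample size); two arms and two sites (Study design); individual 1:1 allocation (Randomisation procedures); significance level 0.05, taken as two-sided because the article does not say. Assumed for the simulations: normal outcomes with SD 1, no treatment effect, patients split at random between the sites, and a reference value of 1.96 unless stated.

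**Formula.** For y = b0 + b1·arm + e, the cluster-robust variance is V = B (Σ_g s_g s_g′) B, with B = (X′X)⁻¹ and s_g the sum of X_i e_i over cluster g.

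**Reading 1: group = arm, no covariates.** The normal equations force the residuals to sum to zero overall and in the treated arm, hence also in the control arm. Both s_g are then zero vectors and V = 0. This is algebra and needs no distributional assumption. Numerically the SE was 3e-17, against an ordinary SE of 0.25 SD in the same data set, and the null was rejected in 100% of 4,000 simulated trials.

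**Reading 1 with one baseline covariate.** The residuals still sum to zero within each arm. Only the covariate part of s_g survives, and it reaches the treatment variance solely through chance imbalance of the covariate between arms. The median SE was about 0.01 SD, with 91% false rejections in 4,000 runs and 90% in a separate 20,000.

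**Reading 2: group = site.** There are two clusters. Their score sums are equal and opposite, so the variance rests on a single contrast. Results from 20,000 null trials:

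| Reference | False rejection |
|---|---|
| 1.96, no correction | 41% |
| 1.96, with the factor G/(G−1) = 2 | 31% |
| t with 1 df (critical value 12.7), no correction | 7% |
| t with 1 df (critical value 12.7), with the factor | 5% |

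The mean SE was 0.15 SD and the median 0.13 SD. The true value is √(2/26) = 0.28 SD. The last row is valid but of little use. At the median SE, the difference needed is 12.7 × √2 × 0.13 = 2.3 SD.

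**Patient as the unit.** With one record per patient and a patient-level robust SE, false rejection was 5.8% (4,000 runs) and 6.2% (20,000 runs), with a mean SE of 0.27 SD. Adding site as a fixed covariate left it at 6.2%.

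**Two eyes, conditional only.** Suppose both eyes of every patient were entered as independent records, with inter-eye correlation ρ. The SE would then be too small by the factor 1/√(1+ρ), and the type I error would be 2Φ(−1.96/√(1+ρ)). The article gives no ρ, so a range is assumed.

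| ρ (assumed) | SE factor | Type I error, formula | Simulated | Simulated, clustered on patient |
|---|---|---|---|---|
| 0.3 | 0.88 | 8.6% | 8.6% | 6.0% |
| 0.5 | 0.82 | 11.0% | 12.2% | 6.1% |
| 0.7 | 0.77 | 13.3% | 15.3% | 6.4% |
| 0.9 | 0.73 | 15.5% | 15.8% | 6.4% |

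**The case against.** *The word is undefined, so the collapse is not stated.* This is correct: the zero standard error follows only if group means arm. The usage in the same paragraph supports that reading without fixing it. But the only other grouping in the article, site, also fails, so the ambiguity does not rescue the sentence.

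*A standard error of 1e-16 would be noticed.* That is likely in the unadjusted model. It is less certain with a covariate or with site as the cluster, where the output looks like an ordinary small standard error.

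*The analysis is exploratory.* This stands and lowers the weight of the point. The analysis is mainly descriptive, the secondary outcomes are declared unpowered, and neither the feasibility proportion nor the SD estimates for a later trial use this variance. The p<0.05 rule keeps the point relevant.

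*A stronger reading: the plan ignores the correlation between a patient's two eyes.* A reader might infer this because blood may be applied to one or both eyes. The article does not support it. The Arm A section says where blood is applied, not which eyes are analysed. The quoted model is for a patient-level outcome, and no section makes the eye the unit of analysis. Choice of study eye is something a condensed article may leave to the full protocol or SAP.

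*A further inference: pooling eyes would give the definitive trial a wrong SD.* This fails on arithmetic. With 52 eyes per arm, E[s²] = σ²(1 − ρ/51). At ρ = 0.8 the SD is low by 1 − √(1 − 0.8/51), about 0.8%.

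**Conclusion.** The clustering statement is wrong as written. No grouping described in the article makes it work. Arm as cluster gives a zero standard error without covariates and about 90% false rejection with one. Site as cluster gives about 41%, or 31% with the small-sample factor, against 1.96. The zero is exact. The other rates rest on simulated normal outcomes with 26 patients per arm and a random split between sites.

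The two-eye figures of about 9% to 16% are a conditional remark. They apply only if both eyes are entered as independent records for secondary ocular outcomes, with an assumed correlation of 0.3 to 0.9.

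The sentence should be corrected before analysis. Because the comparison is exploratory, it falls short of a defect that would undermine the feasibility conclusions.

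**What to change.** In the Data analysis section, delete the words that allow for clustering by group. State that the patient is the independent unit, with ordinary or patient-level robust standard errors, and that site enters as a fixed covariate. With one record per patient, clustering on the patient is the same as an ordinary robust standard error, so deletion is enough for the outcome this sentence covers.

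Add one conditional line: if both eyes of a patient are entered for any secondary ocular outcome, the cluster is the patient.

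The cost is one or two sentences before the analysis starts. No new data are needed and the recruitment target does not change. If a SAP already specifies the patient as the unit, the article's sentence should be brought into line with it.

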### Sample size

As this is a feasibility trial, there were no formal sample size calculations.^23^ The aim of the study is to recruit a sufficient number of patients to evaluate the acceptability and feasibility of the intervention. An outcome of this study will be to estimate parameters such as the SD for a sample size calculation of a subsequent full-scale trial. A sample of 52 patients (26 in each arm) is considered adequate for obtaining reliable sample size estimates.^24 25^ To allow for a conservative attrition rate of 10%, we aim to recruit 60 patients into the trial.

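### Proportional hazards regression is prescribed for a primary outcome that is a proportion without an event time, and 60 patients cannot support the interaction tests planned within those models.

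*Protocol article*

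**What the plan says.** Outcome assessment in the protocol article defines the outcome: "The primary outcome measure is the proportion of eligible patients approached who consent to and comply with the trial protocol". Its listed components are the number eligible, the percentage accepted for randomisation, self-reported adherence and the percentage completing. None is a time to an event.

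Data analysis then sets out four steps that bear on this point:

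- A comparison at a fixed time: "Exploratory efficacy analysis will compare the primary outcome variables derived from the data collected at 8 weeks between the two arms".
- An adjusted time-to-event model for the same outcome: "Secondary analyses of the primary outcome, controlling for baseline covariates, will be performed using proportional hazards regression models".
- A separate analysis: "Analysis of treatment discontinuation adjusted for clinical site, baseline status, and whether the patient is randomised to the FAB or control" (conventional treatment only). This sentence names no model.
- Interactions, stated twice: "Any interaction between baseline status or regimen and treatment will also be assessed", and "Interactions between significant covariates and treatment effects will be assessed in the context of the proportional hazards models".

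The same section accepts p<0.05 as significant and describes the analysis as mainly descriptive.

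On size, the Sample size section says "A sample of 52 patients (26 in each arm) is considered adequate for obtaining reliable sample size estimates" and "To allow for a conservative attrition rate of 10%, we aim to recruit 60 patients into the trial". It gives no power calculation and no expected rate of treatment discontinuation.

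**The concern.** A proportional hazards model needs a time origin, an event and a censoring rule for each person in the analysis. The primary outcome as defined has none of these. It is also measured partly on people who never reach randomisation, so it has no treatment arm over its full denominator. Whoever runs this analysis must either drop it or substitute another outcome for the defined one, and in the second case the result would still be reported as an analysis of the primary outcome.

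The interaction tests raise a separate problem of information. Choosing covariates because they are significant, and then testing their interaction with treatment at 0.05, in a trial of 60 patients will yield either models that do not fit or estimates that range over an order of magnitude. A chance interaction from such a model could be read as a subgroup finding when the definitive trial is designed, although no section says that interaction results will be used for that purpose.

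**Working it through.** **1. Outcome against model.**

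| Needed for a hazard ratio by arm | What Outcome assessment and Data analysis give |
|---|---|
| Event with a time | A yes/no status (consented and complied), summarised as a proportion |
| Time origin and censoring rule | None for this outcome; the arms are compared at a fixed 8 weeks |
| An arm for every person in the denominator | The denominator is eligible patients approached; under Randomisation procedures, allocation follows consent, so decliners have no arm |

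The model does not fit the outcome as defined. No arithmetic is needed for this part.

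**2. The plan's own sample size figure.** Inputs: 52 evaluable patients, 10% attrition, target 60. 52 / 0.90 = 57.8 and 52 × 1.10 = 57.2; both round up to 58. The stated 60 is slightly above this, and I take no issue with it.

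**3. Events needed.** Assumptions: 1:1 allocation (stated), two-sided 0.05 (the level is stated, two-sided is assumed), 80% power (assumed), HR 2 (illustrative). With d events, the variance of the log HR for arm is about 4/d. For an interaction with a binary covariate split evenly, it is about 16/d.

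- Main effect: d = 4 × (1.960 + 0.842)² / (ln 2)² = 4 × 7.849 / 0.4805 = 65.3, so 66 events.
- Interaction (ratio of HRs of 2): d = 16 × 7.849 / 0.4805 = 261.4, so 262 events.

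Each patient contributes at most one event, so the ceiling is 60. At that ceiling the power for the interaction is Φ(√60 × 0.693 / 4 − 1.96) = Φ(−0.62) = 27%. No discontinuation rate makes the test informative.

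**4. What a discontinuation model could carry.** The documents give no discontinuation rate, so I assume 10% to 40% of 60. Five parameters means arm, site, baseline status and two interactions; the number of interactions is also an assumption. CI factors are exp(1.96 × √(4/d)) for arm and exp(1.96 × √(16/d)) for an interaction, each way from the estimate.

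| Events | Per parameter, 3 main effects | Per parameter, 5 terms | CI factor, arm | CI factor, interaction | Power, arm HR 2 |
|---|---|---|---|---|---|
| 6 (10%) | 2.0 | 1.2 | 5.0 | 25 | 13% |
| 8 (60 − 52) | 2.7 | 1.6 | 4.0 | 16 | 16% |
| 12 (20%) | 4.0 | 2.4 | 3.1 | 9.6 | 22% |
| 18 (30%) | 6.0 | 3.6 | 2.5 | 6.3 | 31% |
| 24 (40%) | 8.0 | 4.8 | 2.2 | 5.0 | 40% |

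**5. Whether the models can be fitted.** Cox models were simulated with 60 patients, 8 weeks of follow-up, no true effects, and site and baseline status each binary at 50%. The table shows the share of fits with a diverging coefficient or standard error. A second, independent simulation gave closely similar shares.

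| Expected events | With two interactions | Main effects only |
|---|---|---|
| 6 | 76% | 19% |
| 8 | 58% | 7% |
| 12 | 27% | 1% |
| 18 | 6% | 0% |
| 24 | 1% | 0% |

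The interactions account for most of the failures. At the higher rates the models fit but say little.

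**The case against.** The best defence is that the models are labelled secondary, in a trial with no formal sample size calculation whose analysis is mainly descriptive. Counts and percentages for the primary components are already planned, and no progression decision or primary estimate rests on a hazard ratio. That stands, and it lowers the severity.

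A second defence is that adherence and completion have natural time-to-event versions, and that the full protocol, which is a supplementary file not shown here, may define them. This stands only in part. Time to non-completion or to stopping treatment would be a legitimate outcome, but a different one from the proportion that the article calls primary. Supplying an event time would replace the stated outcome and would not fill in a missing detail.

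A reader might draw four stronger conclusions that the documents do not support:

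- *That the plan expects about six events.* Six is 10% of 60, an allowance for attrition. A patient can stop finger pricks and stay in follow-up, and the intention-to-treat set keeps such patients. The recruitment margin (60 − 52) would give eight. Neither is a discontinuation rate, hence the range above.
- *That a proportional hazards model of discontinuation is the wrong kind of analysis.* The discontinuation sentence names no model; proportional hazards is implied only by the sentences around it. The weakness there is sparse information.
- *That every such model would be uninterpretable.* With main effects only, or at 18 to 24 events, very imprecise is the accurate description.
- *That the event does not exist in Arm B.* The text refers to treatment discontinuation, not to stopping FAB. Arm B receives conventional therapy, which can be stopped, and most of the listed withdrawal reasons can arise in either arm.

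**Conclusion.** The concern holds in two parts. First, the stated model and the stated primary outcome are incompatible. This follows from the article's own wording and rests on no numerical assumption. Second, the planned interaction tests cannot be informative in 60 patients. This rests on two-sided 0.05, 80% power, an illustrative ratio of 2 and a balanced binary covariate, but not on any discontinuation rate, because the requirement of about 262 events is more than four times the number recruited (262 / 60 = 4.4).

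How badly a discontinuation model would behave does depend on an assumed rate and an assumed five-term model, and runs from often non-estimable at 6 to 8 events to very imprecise at 24. The severity is should-fix: the error is plain and cheap to remove, but it affects secondary analyses in a feasibility trial.

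**What to change.** - Delete the sentence that applies proportional hazards regression to the primary outcome, and both interaction statements.
- Report the components of the primary outcome as proportions with 95% CIs, each on its proper denominator: consent among eligible patients approached; adherence and completion among those randomised, by arm.
- Describe treatment discontinuation by arm with counts, timing, reasons and exact 95% CIs for the proportions.
- If a time-to-discontinuation model is kept, define it as a separate outcome with its own event, time origin and censoring rule, and limit it to an exploratory arm effect without interactions.

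The cost is the loss of exploratory models that the data cannot support. No extra data are needed for the proportions and counts, the analysis becomes shorter, and it then matches the descriptive intent stated in the Data analysis section.
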